**Figure 2 figure2:**
[figure not shown]
Intervention steps in the jail-to-community continuum. DCJ: Dallas County Jail; EHR: electronic health record; PrEP: pre-exposure prophylaxis; STI: sexually transmitted infection.

In the “identify” step, when individuals enter the jail, a jail EHR record will be created (or an existing record will be opened for those with prior DCJ incarceration). Our automated algorithm will match the jail EHR to the Parkland EHR and generate an individual HIV risk score. For people with predicted HIV risk above a prespecified threshold that maximizes sensitivity without causing alert fatigue among providers, an automated prompt will appear in the jail EHR for providers to discuss PrEP and order HIV/STI testing. As illustrated in Figure 2, providers will also be prompted to order HIV/STI tests for any patients who report risk factors at intake or during a clinical assessment (eg, transgender identity and requests to be housed with MSM) or who request testing directly. Prompts will persist until orders are completed as a “nudge,” a behavioral economic intervention to maximize ordering [83], and results are entered into the EHR.

In the “engage” step, positive HIV tests will prompt referrals to the jail HIV clinic for rapid initiation of antiretroviral therapy according to the current practice, and STIs will be treated based on CDC guidelines [84]. Persons with negative HIV tests will meet one-on-one with a provider or PrEP navigator and receive counseling informed by our PrEP decision-support tool. The navigator we hire will be experienced in working with CL-involved people. Counseling will be person-centered and culturally tailored, with positive sexual health framing.

In the “navigate” step, for patients interested in PrEP, the navigator will review a list of PrEP clinic locations and assist with selecting a provider. Once an individual is released from the DCJ, the navigator will facilitate PrEP linkage by contacting that individual (by phone or SMS text messaging) and providing personalized care navigation. A hotline will be available for released individuals to call for assistance with PrEP referrals. The navigator will continue to follow referred patients for 3 months after any PrEP initiations, recording these contacts and clinical outcomes in REDCap, a secure online data capture system [85].

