##### Effectiveness Regarding New HIV/STI Diagnoses

We will also track STIs and new and previously known HIV diagnoses in the jail among priority groups and the general jail population. STI positivity will be calculated as positive tests per the total number of tests completed. New HIV diagnosis rates will be calculated as confirmed positive test results in persons without a prior diagnosis of HIV per the total number of tests completed within a given time period. We will use an interrupted time series analysis using monthly data points to compare rates during the 24 months before and 24 months after our intervention is implemented. Our primary analysis will involve a comparison of the longitudinal rates before and after the intervention, and a mixed effects model for interrupted time series will be used as a secondary analysis. We will conduct linear regression analyses to determine if there is a significant difference in new HIV diagnosis rates before and after the intervention.

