##### Sustainment

Sustainability refers to the extent to which a new practice is maintained or institutionalized within a setting’s ongoing operations [86]. We will assess how well the strategy components are maintained as part of existing jail processes for 6 months after the formal 24-month study period, including tracking retention in PrEP care for up to 6 months (through navigator follow-up). Our research team includes dissemination consultants, who are medical providers working in jails in Austin, TX; Chicago, IL; and Boston, MA, and who will offer input on refining our strategy components for ongoing use at the DCJ and the potential transfer and integration into other jail settings.

For PrEP linkage, current rates of linkage are essentially zero. Thus, in lieu of a pre/post comparison, we will report the proportion of patients linked to PrEP care during the implementation period with 95% CIs. Power analysis is performed for the interrupted time series analysis of monthly HIV positivity rates, assessing the difference in the mean between the 24 months before and after implementation. Over the preimplementation period, an anticipated 250 tests will be performed monthly with 3 new HIV diagnoses per month. In the postimplementation period, of 500 HIV tests per month, an increase to 9 new diagnoses per month is anticipated due to the focus on individuals identified by the prediction model as being at increased HIV risk. Furthermore, we assume a correlation of 0.2 among monthly observations. Based on a mixed effects Poisson regression model, we can detect the difference in the mean HIV-positive rate between the 2 periods with >80% power at a 2-sided type I error of 0.05. We will also perform subgroup analyses, comparing testing rates by sex, age group, and race or ethnicity.

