## Discussion

### Expected Results

We anticipate that the implementation of the multicomponent strategy will promote robust linkage to PrEP care for many individuals at risk for HIV, which currently does not occur at the DCJ. Moreover, we expect to identify a higher number of new HIV infections and STIs than in the 2 years prior to implementation. Our final product will be a well-integrated sustainable multicomponent PrEP implementation strategy that starts upon jail entry and ends with linkage to community-based HIV prevention, which can address major HIV-related inequities for CL-involved populations.

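### The before/after test uses diagnoses per test completed, which measures testing yield and does not test the stated expectation that more infections will be found

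*Protocol article*

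**What the plan says.** Under Effectiveness Regarding New HIV/STI Diagnoses, the protocol article defines the HIV outcome as confirmed positives "in persons without a prior diagnosis of HIV per the total number of tests completed within a given time period". For STIs, "STI positivity will be calculated as positive tests per the total number of tests completed". It then states: "We will use an interrupted time series analysis using monthly data points to compare rates during the 24 months before and 24 months after" the intervention.

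The power statement, placed under Sustainment, applies to monthly HIV positivity. Before implementation, "an anticipated 250 tests will be performed monthly with 3 new HIV diagnoses per month". Afterwards, "of 500 HIV tests per month, an increase to 9 new diagnoses per month is anticipated", and the article says this is "due to the focus on individuals identified by the prediction model as being at increased HIV risk". Steps for Strategy Implementation describes the mechanism: when predicted risk passes a threshold, "an automated prompt will appear in the jail EHR for providers to discuss PrEP and order HIV/STI testing", and prompts stay until orders are completed.

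Expected Results states the hypothesis as a number: "we expect to identify a higher number of new HIV infections and STIs than in the 2 years prior to implementation".

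**The concern.** The intervention acts on the denominator of the tested rate in two ways: it raises the number of tests, and it shifts testing toward people flagged as higher risk. Both changes start at the interruption, so the time-series design cannot separate them from the effect being estimated. The rate moves only by the ratio of diagnoses to tests, whereas the expectation concerns diagnoses alone.

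A programme that finds clearly more infections, but fewer than planned, could therefore return a null result or an apparent decline in the only before/after comparison for which power is given. The article sets out no formal analysis of diagnosis counts, or of diagnoses per person entering the jail, that would show the gain.

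**Working it through.** **Inputs.** From Sustainment: 250 tests and 3 diagnoses per month before, 500 tests and 9 diagnoses per month after, two-sided alpha 0.05, power above 80%. From Effectiveness Regarding New HIV/STI Diagnoses: 24 months in each period. From Study Setting: 51,000 incarcerated individuals per year.

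**Reproducing the plan's figure.** The rates are 3/250 = 1.2% and 9/500 = 1.8%, a ratio of 1.5. Events are 24 × 3 = 72 and 24 × 9 = 216. The standard error of the log ratio is √(1/72 + 1/216) = 0.1361. Then ln(1.5)/0.1361 = 2.98, and power is Φ(2.98 − 1.96) = 84.6%. The claim of more than 80% holds for independent months. The article assumes a correlation of 0.2 without giving its structure. Power is 91.5% if the correlation is a common random effect that cancels in the contrast, and 68.9% if it is first-order autoregressive within each period.

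**Break-even.** The per-test ratio is (D/500)/(3/250) = D/6, where D is diagnoses per month afterwards. It is below 1 whenever D is below 6. If the first 250 tests still yield 3 diagnoses, break-even means the extra 250 tests yield 3 (1.2%, the baseline). The plan needs them to yield 6 (2.4%).

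**Range of outcomes.** The method is the same, with SE = √(1/72 + 1/(24D)). The count columns assume equal jail intakes in both periods, so the offset cancels and the ratio is D/3. Only D = 9 is a planning value; the other rows are illustrations.

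| D per month | Per-test rate | Per-test ratio | Power, per test | Count ratio | Power, counts |
|---|---|---|---|---|---|
| 4 | 0.8% | 0.67 | 73.9%, for a decline | 1.33 | 45.4% |
| 5 | 1.0% | 0.83 | 23.1%, for a decline | 1.67 | 92.9% |
| 6 | 1.2% | 1.00 | 5% (alpha) | 2.00 | 99.8% |
| 7.5 | 1.5% | 1.25 | 36%, for a rise | 2.50 | >99.9% |
| 9 | 1.8% | 1.50 | 84.6%, for a rise | 3.00 | >99.9% |

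Simulation with independent Poisson months agrees. At D = 5 the estimate is a decline in 88% of runs and a significant decline in 24%. At D = 4 the decline is significant in about 73%. Power of 80% for a rise in the per-test rate needs about 8.8 diagnoses per month, 2.9 times baseline.

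**Per-intake scale.** 51,000/12 = 4,250 per month, so the planned contrast is 3/4,250 = 0.71 against 9/4,250 = 2.12 per 1,000. The level of this denominator does not affect the ratio of 3; only its stability does.

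**The case against.** Positivity per test is a recognised measure of yield, and directing tests to higher-risk people is what the strategy sets out to do. If the extra tests find infections at no more than the baseline 1.2%, then targeting did not improve yield, and a flat rate answers that question correctly. All of this stands, and it is why positivity should be kept.

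Much of the needed information is also collected. Table 1 lists new diagnoses without a denominator and lists testing offered and completed separately. Diagnoses are tracked in priority groups and in the general jail population. A reader could separate volume from yield descriptively, but the formal test does not do so.

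A rate per intake has the opposite weakness. Doubling tests at unchanged positivity gives a ratio of 2, detected with 99.8% power, and so scores volume alone as success. This stands too: it should not simply replace positivity.

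Three stronger readings are tempting, and the article does not support them. One is that the result cannot be read as effectiveness at all. If positivity rises and test volume does not fall, more infections were found, and that is the case on the plan's own figures. Another is that this is the study's only comparison. Subgroup comparisons are planned, feasibility and acceptability have thresholds, and PrEP linkage is reported with confidence intervals. The third is that the power statement is an arithmetic error, yet it reproduces under independent months.

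**Conclusion.** The concern holds as a mismatch between the tested measure and the stated expectation. On the plan's volumes, any rise from 3 to fewer than 6 diagnoses per month lowers the tested rate, and exactly 6 leaves it unchanged. At the planned 9 the test works as described. A null or reversed result is therefore a possibility and not what the plan predicts. The same reasoning applies to STI positivity, but the article gives no STI test volumes from which to size it.

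The break-even rests on the 250 and 500 monthly tests and the baseline of 3 diagnoses. The power figures assume independent Poisson months, and the count comparison also assumes stable intakes. The figure of 4,250 per month comes from individuals per year. People return to the jail, so intakes will differ from it.

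**What to change.** Before post-implementation data are analysed:

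- Prespecify an interrupted time series of monthly new-diagnosis counts with a log(jail intakes) offset, for HIV and for each STI, as the test of the expectation in Expected Results.
- Keep positivity per test as the yield measure and report monthly test volume beside it. State that neither the per-intake rate nor positivity will be interpreted alone.
- Where feasible, apply one fixed version of the risk model to both periods and report positivity within the same model-defined risk strata.
- Describe the result as case-finding.

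The cost is protocol or analysis-plan wording, a monthly count of intakes (not individuals) from the jail EHR, and retrospective scoring of the earlier period if the stratified report is done. The downside is that the per-intake rate also reflects testing coverage, which is why volume and positivity must accompany it.

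### The new-HIV-diagnosis outcome is given incompatible analyses, with no trend term or correlation structure fixed for the primary test, and the >80% power does not apply to an interrupted time series effect

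*Protocol article*

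**What the plan says.** The section Effectiveness Regarding New HIV/STI Diagnoses (Protocol article, Aim 3) makes four statements about this outcome:

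- The general approach: "We will use an interrupted time series analysis using monthly data points". The series covers two years on each side of go-live.
- The primary analysis: "Our primary analysis will involve a comparison of the longitudinal rates before and after the intervention".
- The secondary analysis: "a mixed effects model for interrupted time series will be used as a secondary analysis".
- The significance test: "We will conduct linear regression analyses to determine if there is a significant difference in new HIV diagnosis rates before and after the intervention".

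The power paragraph stands under Sustainment. It describes itself as power for the interrupted time series, but the quantity assessed is the difference in mean between the two 24-month periods. Its inputs are "an anticipated 250 tests will be performed monthly with 3 new HIV diagnoses per month" before go-live and, afterwards, "of 500 HIV tests per month, an increase to 9 new diagnoses per month is anticipated". It assumes that monthly observations correlate at 0.2, without saying how. "Based on a mixed effects Poisson regression model", it claims more than 80% power at two-sided 0.05.

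**The concern.** One outcome carries a before/after comparison, a mixed effects time-series model, a linear regression and a mixed effects Poisson model, and nothing says how they relate. The model behind the power figure is not the one named for the test.

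Two consequences follow.

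- **Trend.** There is one jail and no control series, so modelling the trend is the main protection against calendar time. A contrast of period means has none: drift in positivity that began before go-live is counted as effect. The Discussion expects more new infections than in the two years before implementation, and drift alone could produce that.
- **Correlation.** The power paragraph assumes correlated months, but no error structure is attached to the linear regression. If the correlation is serial, ordinary standard errors are too small.

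**Working it through.** **Inputs from the article.** 24 months per period. Before: 3/250 = 1.2% per month, 24 × 3 = 72 diagnoses. After: 9/500 = 1.8% per month, 24 × 9 = 216 diagnoses. Rate ratio 1.5, log 0.405. Correlation 0.2, structure unstated. Alpha 0.05 two-sided.

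**Step 1: the stated power.** For a Wald test of the log rate ratio, SE = √(VIF × (1/72 + 1/216)) and power = Φ(0.405/SE − 1.96). The variance factor (VIF) depends on what 0.2 means:

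| Reading of the 0.2 | VIF | SE | Power |
|---|---|---|---|
| Independent months (0 instead of 0.2) | 1 | 0.136 | 85% |
| Exchangeable over all 48 months | 1 − 0.2 = 0.8 | 0.122 | 91% |
| AR(1) | 1.2/0.8 = 1.5 | 0.167 | 68% |
| Exchangeable within each period only | 1 + 23 × 0.2 = 5.6 | 0.322 | 24% |

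A two-proportion check on 6,000 and 12,000 tests gives 87%. So the stated >80% is reproduced for a difference in means with independent or fully exchangeable months, but not under the other two readings.

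**Step 2: size of the linear regression.** Under AR(1) 0.2 a nominal 5% before/after test rejects with probability 2 × (1 − Φ(1.96/√1.5)) = 11.0%. Simulation of 48 points gives 10.7%. With exchangeable correlation over all months it gives 5.0%; with correlation within period only, 45%. Segmented ordinary least squares under AR(1) 0.2 still rejects 10–11%. The inflation therefore comes from unmodelled serial correlation, and adding time terms does not remove it.

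**Step 3: drift without a time term.** The documents give no trend, so the drift is an assumption. With drift d per month on the log scale and no true effect, period midpoints are 24 months apart, so the spurious rate ratio is exp(24d). Expected diagnoses are 72 before and 12,000 × 1.2% × exp(24d) = 144 × exp(24d) after.

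| Assumed drift | Spurious rate ratio | SE | False positives |
|---|---|---|---|
| +0.5% per month | 1.13 | √(1/72 + 1/162) = 0.142 | 13% |
| +1% per month | 1.27 | √(1/72 + 1/183) = 0.139 | 41% |
| +1.5% per month | 1.43 | √(1/72 + 1/206) = 0.137 | 75% |

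Simulations at +1% per month gave 41–47%, depending on set-up. With a segmented Poisson model and independent months, the rate falls to about 4–5%. On a yearly scale, simulated independent months without a time term gave false-positive rates of about 12%, 31% and 84% at +5%, +10% and +20% per year, and 22% at −10% per year.

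**Step 4: power for a step once trend is modelled.** From the Poisson information with monthly means of 3 and 9, and a 1.5-fold step:

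- Common slope: SE 0.245, power Φ(0.405/0.245 − 1.96) = 38%.
- Step plus slope change: SE 0.277, power Φ(0.405/0.277 − 1.96) = 31%.
- AR(1) 0.2 (SE × √1.5): 27% and 22%. A second calculation gave 24–29%, so the range is 22–29%.

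**Step 5: does a standard repair work?** Uncorrected Newey-West errors on the segmented Poisson model, 48 months, no effect: the step test rejects about 8–16% at zero correlation and 14–18% under AR(1) 0.2, depending on lag. That is no better than the linear regression and may be worse.

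**The case against.** The strongest reply is that the sentence governing the section promises an interrupted time series, that the primary comparison is of longitudinal rates, and that linear regression may mean segmented regression, a common way to fit such a series. Time terms and error structure are details that an article may leave to the full protocol or SAP.

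Much of this limits what can be claimed. A reader might infer any of the following, and the documents do not support them:

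- **That the primary analysis is a raw before/after contrast and the time series is abandoned.** A time term is neither stated nor excluded, and only the mixed effects version is made secondary.
- **That the test has 11% type I error under the plan's own assumption.** The plan gives 0.2 without a structure. AR(1) is one reading, and it does not reproduce the plan's >80%; full exchangeability does, and leaves the test at 5%.
- **That linear regression, few events or unequal test volumes cause the inflation.** With independent months the before/after linear test holds about 5%. Unequal denominators mainly cost efficiency.
- **That a mixed model has nothing to work with.** The article tracks priority groups as well as the general jail population, so strata exist, and correlated-error forms are possible. The article does not say which is meant.

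The core survives. The objection does not explain why the time-series model is listed separately as secondary, or why power labelled for the time series is computed for a difference in means under another model. Those are conflicts in the text, not omitted detail.

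**Conclusion.** The analyses named for new HIV diagnoses are incompatible as written and must be reconciled. A comparison of period means in this uncontrolled single-jail design is open to drift: a spurious ratio of 1.27 and about 41–47% false positives at an assumed +1% per month. Those figures illustrate the exposure; they are not estimates for this jail.

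The size of the linear regression is conditional: about 11% under AR(1) 0.2, 5% if the 0.2 is exchangeable over all months. The >80% power holds for a difference in means under independent or fully exchangeable months. It does not apply to a step effect with trend terms, where power is about 31–38% with independent months and 22–29% under AR(1) 0.2.

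The problem concerns one effectiveness outcome. PrEP linkage, reported as a proportion with a 95% CI, is unaffected.

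**What to change.** - **Name one primary model:** segmented Poisson regression (negative binomial if overdispersed) of monthly confirmed new diagnoses, with a log(tests) offset, a calendar-month trend, a step at go-live and a slope change.
- **State the correlation structure** meant by 0.2. Handle it with a model-based AR(1) or another small-sample-valid method, checked by simulation at 48 points. Do not rely on uncorrected Newey-West errors, which over-reject at this length.
- **Keep the before/after rate ratio as descriptive.** Remove the linear regression and mixed-effects wording, or make both explicitly subordinate.
- **Restate power for the named model.** If the difference-in-means figure stays, label it as such and give the correlation reading on which it depends (about 68% under AR(1) 0.2).

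The cost is wording, a short simulation and a much lower stated power for a 1.5-fold step. Switching to a per-booking denominator to recover that power is not a remedy: the article defines the rate per test completed, and a per-booking rate would also count the planned doubling of tests, which is a different estimand.

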##### Sustainment

Sustainability refers to the extent to which a new practice is maintained or institutionalized within a setting’s ongoing operations [86]. We will assess how well the strategy components are maintained as part of existing jail processes for 6 months after the formal 24-month study period, including tracking retention in PrEP care for up to 6 months (through navigator follow-up). Our research team includes dissemination consultants, who are medical providers working in jails in Austin, TX; Chicago, IL; and Boston, MA, and who will offer input on refining our strategy components for ongoing use at the DCJ and the potential transfer and integration into other jail settings.

For PrEP linkage, current rates of linkage are essentially zero. Thus, in lieu of a pre/post comparison, we will report the proportion of patients linked to PrEP care during the implementation period with 95% CIs. Power analysis is performed for the interrupted time series analysis of monthly HIV positivity rates, assessing the difference in the mean between the 24 months before and after implementation. Over the preimplementation period, an anticipated 250 tests will be performed monthly with 3 new HIV diagnoses per month. In the postimplementation period, of 500 HIV tests per month, an increase to 9 new diagnoses per month is anticipated due to the focus on individuals identified by the prediction model as being at increased HIV risk. Furthermore, we assume a correlation of 0.2 among monthly observations. Based on a mixed effects Poisson regression model, we can detect the difference in the mean HIV-positive rate between the 2 periods with >80% power at a 2-sided type I error of 0.05. We will also perform subgroup analyses, comparing testing rates by sex, age group, and race or ethnicity.

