## Methods

### Study Setting

The DCJ is the main jail facility for Dallas County, with 51,000 incarcerated individuals per year (86% men, 48% Black, and 30% Hispanic) and approximately 275 individuals entering and leaving the jail daily. The mean length of stay is 45 days, and 11% of people transfer to prison [65]. Parkland Health, a teaching hospital for UT Southwestern Medical Center, provides health care services at the jail for approximately 6200 patients monthly. Health care for individuals experiencing incarceration is paid for by Dallas County.

Of over 12,000 HIV/STI tests performed each year at the DCJ, there are approximately 50 to 100 new HIV diagnoses (personal communication by [name], April 2024) and high STI positivity (5% syphilis, 5% gonorrhea, and 11% chlamydia) [35,66], which is a recommended indication for PrEP use. The approach to HIV testing at the DCJ is a combination of opt-in and opt-out. All persons entering the jail complete a nursing intake questionnaire to review medical history, receive the option for HIV/STI testing (opt-in), and, for men, indicate if they want to be in separate housing for MSM as a safety precaution. All individuals who undergo blood draws are offered opt-out HIV testing. Individuals with negative HIV test results are not routinely counseled about the results, and few, if any, receive information about PrEP. Currently, new initiation of PrEP is not permitted at the DCJ, and thus, the study will focus on linkage to PrEP after release.

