## Results

The study was funded by the National Institute of Mental Health in April 2022. Progress has been made on various aims to date. Qualitative interviews have been completed with 26 individuals, including 9 formerly incarcerated individuals, 9 county jail staff, and 9 employees of community organizations (1 individual was both a formerly incarcerated individual and an employee of a community organization). A focus group with 10 additional individuals has also been conducted. All interviews have been transcribed, coded, and analyzed, and a manuscript highlighting the key themes is in progress.

In addition, summaries of field notes for each interview have been organized into key barriers; facilitators; suggested approaches to overcome barriers; resources needed to overcome barriers; and specific strategies to improve risk assessment, HIV testing, sexual health or PrEP education during incarceration, and postrelease linkage to PrEP. Findings from these interviews have been applied to formulate a jail PrEP implementation protocol using rapid qualitative analysis.

An HIV risk prediction model based on jail EHR data to identify individuals most likely to benefit from PrEP has been developed using records from 33,458 individuals who have undergone HIV testing in jail. This model has been optimized using machine learning, has been internally validated, and is ready to be deployed. Future exercises will include integration with health system EHR data from Parkland Hospital and comparisons to parsimonious models, which will guide the iterative development of the model. We anticipate that preliminary study findings on the implementation and effectiveness of the jail PrEP implementation strategy will be available in 2026. 

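### The power analysis assumes 36 new HIV diagnoses a year before implementation, below the 50 to 100 a year that the protocol reports for the same jail, and the two are not reconciled

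*Protocol article*

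**What the plan says.** In the protocol article, the power analysis stands under Sustainment. For the period before implementation it takes "an anticipated 250 tests will be performed monthly with 3 new HIV diagnoses per month". For the period after, "of 500 HIV tests per month, an increase to 9 new diagnoses per month is anticipated", and the rise is attributed to concentrating on people whom the prediction model flags. The text adds that "we assume a correlation of 0.2 among monthly observations" and concludes that the difference can be detected "with >80% power at a 2-sided type I error of 0.05".

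The outcome is a rate, not a count. The section on effectiveness regarding new HIV/STI diagnoses defines it as confirmed new positives "per the total number of tests completed within a given time period", and the plan is to "compare rates during the 24 months before and 24 months after our intervention is implemented".

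The Study Setting section describes current practice at the same jail: "Of over 12,000 HIV/STI tests performed each year at the DCJ, there are approximately 50 to 100 new HIV diagnoses". The diagnosis range is sourced to a personal communication of April 2024.

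**The concern.** Three diagnoses a month is 36 a year. The protocol's own account of the jail puts the figure at 50 at the least and 100 at the most. The power paragraph does not say that its baseline refers to a subgroup, an earlier period or a different case definition, so a reader must take both figures as describing new HIV diagnoses at this jail before the strategy starts.

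The assumed effect, positivity rising from 1.2% to 1.8%, is built on the lower figure. This is the only power statement in the article, and it supports the before-and-after comparison of new HIV diagnosis rates. If the baseline diagnosis count is wrong, the assumed rate ratio and the stated power change with it, unless the test denominator is wrong in the same proportion.

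**Working it through.** **Inputs.** Sustainment: 3 diagnoses and 250 tests a month before; 9 and 500 after; two-sided alpha 0.05. Effectiveness section: 24 months in each period. Study Setting: 50 to 100 new HIV diagnoses a year; over 12,000 HIV and STI tests a year, pooled.

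**1. The plan's own figure.** Over 24 months the inputs give 3 × 24 = 72 diagnoses in 6,000 tests (1.2%) and 9 × 24 = 216 in 12,000 (1.8%). With a Wald test on the log rate ratio for independent Poisson counts:

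- rate ratio (RR) = 0.018 / 0.012 = 1.5, and ln 1.5 = 0.405
- SE = √(1/72 + 1/216) = 0.136
- z = 0.405 / 0.136 = 2.98
- power = Φ(2.98 − 1.96) = 0.846

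The claim of more than 80% is reproduced. This check ignores the 0.2 correlation, whose structure the article does not state. A shared random effect that cancels between periods (variance × 0.8) gives 0.915, and a first-order autoregressive structure (variance × 1.5) gives 0.682.

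**2. The diagnosis counts side by side.**

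- Power analysis: 3 × 12 = 36 a year.
- Study Setting: 50/12 = 4.17 to 100/12 = 8.33 a month.
- Shortfall against the lower end: (50 − 36)/50 = 28%.
- The post-implementation figure, 9 × 12 = 108 a year, is 108/100 = 1.08 to 108/50 = 2.16 times the reported current count. It is 3 times the assumed one.

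**3. The test counts side by side.** 250 × 12 = 3,000 HIV tests a year, against over 12,000 HIV and STI tests together. If HIV, syphilis, gonorrhea and chlamydia tests contributed equally (an assumption), HIV tests would be 12,000/4 = 3,000 a year, exactly 250 a month. The Results section mentions "records from 33,458 individuals who have undergone HIV testing in jail" without the period. Over an assumed 7 to 14 years that is 33,458/84 = 398 down to 33,458/168 = 199 people a month, the same order as 250. So 250 HIV tests a month is not contradicted. HIV-only volume is unknown, and I take 250 to 1,000 a month as the range.

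**4. What the reported diagnosis counts do to the power.** The post period is held at 9/500. Baseline positivity is monthly diagnoses divided by monthly tests, RR is 1.8% divided by that, and power is computed as in step 1.

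| HIV tests/month before | 50 diagnoses/year | 75/year | 100/year |
|---|---|---|---|
| 250 | 1.67%, RR 1.08, power 0.10 | 2.50%, RR 0.72 (a fall) | 3.33%, RR 0.54 (a fall) |
| 500 | 0.83%, RR 2.16, power 1.00 | 1.25%, RR 1.44, power 0.93 | 1.67%, RR 1.08, power 0.12 |
| 1,000 | 0.42%, RR 4.32, power 1.00 | 0.63%, RR 2.88, power 1.00 | 0.83%, RR 2.16, power 1.00 |

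For the top left cell: 100 events before and 216 after, SE = √(1/100 + 1/216) = 0.121, ln 1.08 = 0.077, z = 0.64, power 0.098.

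**5. Where 80% power for an increase is reached.** The requirement is ln RR ≥ (1.96 + 0.84) × SE. At 50 a year, SE = 0.121, so RR must be at least 1.40. Baseline positivity is then at most 1.8%/1.40 = 1.28%, which needs 4.17/0.0128 = about 325 HIV tests a month. The same steps give about 468 at 75 a year and about 609 at 100 a year. At the stated 250 the requirement fails across the whole range. At 609 or 1,000 it is met, but 500 tests a month after implementation would then be fewer than before.

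**The case against.** - **The test figures do not contradict each other.** A reader might infer that 3,000 tests a year clashes with over 12,000. The documents do not support that: the larger figure pools HIV with STI tests, and an equal four-way split gives 250 a month. This objection stands in full. It does not touch the diagnosis gap, because the 50 to 100 are HIV diagnoses only.
- **The low-power scenario mixes sources.** A reader might infer that the assumed effect does not exist or that positivity should be expected to fall. That result needs the Study Setting diagnoses over the power analysis's 250 tests, a pairing the article never makes. If the pooled 12,000 were all HIV tests, the RR would be 2.16 to 4.32 and power near 1.00. This stands: the direction is indeterminate.
- **Counts are not the outcome.** Comparing 9 with 8.33 diagnoses a month (ratio 1.08, power 0.12) suggests a lack of power, but the planned outcome is a rate per test, and at the other end of the range 9 against 4.17 gives power near 1.00. This stands, and I place no weight on count-only power.
- **The figures may differ in date or population.** The higher range dates from April 2024, while funding came in April 2022. Table 1 reports its metrics among high-risk patients, so 250 and 3 might be such a subset. Either is possible, but the power paragraph says neither, and it mentions the model-based focus only as the reason for the later rise. Since the model is described as ready to be deployed, the April 2024 figure appears the closer to the pre-implementation months.
- **Little hangs on it.** In a type 3 hybrid study this is one effectiveness outcome, and the calculation sets no enrolment target. That limits the consequence to the credibility of one comparison and its only power statement.

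**Conclusion.** The point holds for the diagnosis baseline. The power analysis assumes 36 new diagnoses a year where the protocol reports about 50 to 100, at least 28% too few on its own figures, and no text reconciles them. The arithmetic of the power statement is sound (about 0.85 under independence). The input is what is in dispute.

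The effect on power cannot be fixed from the article, because HIV-only test volume is missing. With the post period at 9/500 and independent Poisson counts, it runs from about 10% (RR 1.08), or a reversed direction (down to RR 0.54), at 250 tests a month, to near 1.00 at 1,000. In the second case the planned 500 tests a month would halve testing. The finding is therefore neither that the study is underpowered nor that positivity will fall. It is that the more-than-80% claim rests on a baseline the protocol itself contradicts.

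**What to change.** - Replace 250 and 3 with the observed monthly HIV-only tests and confirmed new diagnoses from the jail EHR for the pre-implementation months, in the same population and with the same test definition as the analysis.
- Revise the post-implementation assumption (500 and 9) to match.
- Restate the power, showing it over 4.2 to 8.3 diagnoses a month and over the plausible range of HIV-only test volume.
- If 250 and 3 describe a high-risk subset, say so, and define the same subset in the pre-period by scoring those records retrospectively. Otherwise the comparison mixes a change in who is tested with the effect of the strategy.
- State HIV-only test volume in the Study Setting section so that the two sections can be read together.

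The cost is one EHR query and a rewritten power paragraph. The stated power may become less favourable.
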